## Secondary outcome measures

### Efficacy

Psychological distress: The Kessler Psychological Distress Scale (K10) is a reliable (*α* = 0.93), validated, 10-item unidimensional self-report measure of participant mental distress [33] often used by clinicians as a screening tool and marker of eligibility for government-funded support services. Respondents indicate from 1 to 5 how much a given statement was true for them in the past 4 weeks with total possible scores of 10–50 (lower scores indicate less distress). The GP or a study nurse will administer the K10 to potential participants as a screening material to aid in confirming eligibility, and then at 3 months post-baseline, 6 months post-baseline, and 9 months post-baseline.Personal recovery: The Recovery Assessment Scale—Domains and Stages (RAS-DS) [18] is a reliable (*α* = 0.96), validated, 38-item multidimensional self-report measure of personal recovery designed to measure the recovery-oriented impact of services provided to participants. The scale is constructed of five domains relevant to recovery goals, with respondents indicating how much a given statement is true for them from 1 to 4. Higher scores in each domain or stage indicates areas the person feels more confident about as part of their recovery. The RAS-DS is routinely used by peer workers as a descriptive tool. This tool will be used to inform intervention efficacy for participants at baseline, 3 months post-baseline, 6 months post-baseline, and 9 months post-baseline.Satisfaction with service: The Your Experience of Service (YES) is a descriptive short-form (21-item) version of the Australian YES [34] tailored to evaluating CMOs. The YES is used in evaluating services delivered by government and non-government healthcare providers in Australia. Respondents indicate their experiences from 0 to 5 across three areas (higher score indicates more satisfaction with a service). The measure then prompts responses to open-ended questions for further information. This measure will be completed during the participant’s final session.

### Health outcomes and health services utilisation

Quality of life years: The European Quality of Life 5-Dimension 5-Level scale (EQ-5D-5L) [35] is a reliable (*α* = 0.82), validated, 5-item multidimensional measure commonly used in the field of health economics to estimate the number of quality-of-life-years resulting from an intervention to predict future costings. Respondents indicate which statement they agree with most regarding their health ‘today’ for five health domains with lower scores indicating better health. Respondents also provide an indicator of their general health on a scale of 1–100 (higher scores indicate better health). This measure will be used to inform the intervention efficacy in terms of prospective healthcare cost-reduction at baseline, 3 months post-baseline, 6 months post-baseline, and 9 months post-baseline.Healthcare service use.A 12-item questionnaire developed for this study will be used to collect information about participant health resource use. The questionnaire is specific to the socio-economic status of participants and costs incurred from accessing services and treatments (e.g., service and treatment costs). This measure will be used to provide context to findings around intervention efficacy in terms of healthcare costs at baseline, 3 months post-baseline, 6 months post-baseline, and 9 months post baseline.Burden experienced by family members or carers: The Burden Scale for Family Caregivers (BSFC-s) [36, 37] is a widely used reliable (*α* = 0.92), validated, ten-item unidimensional self-report measure of subjective carer burden amongst family caregivers. Responders indicate agreement with statements on a scale from 0 (strongly disagree) to 3 (strongly agree), with total possible scores of 0–30 (lower scores indicate lower carer burden). This measure will be used to inform intervention efficacy in terms of ongoing effects for participating family members or carers at baseline, 3 months post-baseline, 6 months post-baseline, and 9 months post-baseline.

### Evaluation of intervention

Stakeholders from a range of perspectives (participants, peer workers, family members or carers, and practice staff) will be invited to take part in evaluating the intervention in terms of efficacy and acceptability.Effectiveness and acceptability.Perceived effectiveness of intervention will be measured using a scale adjusted for this purpose. This scale will follow the generic form of the TFA acceptability questionnaire, which is an eight-item theory-informed self-report measure of the acceptability of healthcare interventions [31]. Constructs consider affective attitudes, burden, ethical consequences, perceived effectiveness, coherence, self-efficacy, opportunity costs, and overall acceptability of an intervention. Responders indicate agreement with statements on a scale from 1 to 5, with total possible scores of 8–40 (higher scores indicate higher acceptability). This measure will be completed during the participant’s final session.Attitude toward peer workers.Practice staff attitude toward peer workers will be measured using the affective attitude item from the generic form of TFA acceptability questionnaire, which asks either ‘Did you like or dislike [intervention]?’ (participants indicate from 1 (strongly dislike) to 5 (strongly like)) or ‘How comfortable did you feel [behaviour e.g., to engage with] [intervention]?’ (participants indicate from 1 (very uncomfortable) to 5 (very comfortable)) where [intervention] refers to peer workers [31]. This measure will be completed after the final participant has completed the intervention.Qualitative assessment.Approximately 6 months after the PS-PC has launched, all participants will be invited via email to take part in interviews of approximately 30 min in length. Peer workers and practice staff will also have the option of participating in a focus group of approximately 1.5 h. Interviews and focus groups will follow a guide developed in reference to CFIR and RE-AIM frameworks. Verbal informed consent will be obtained by the administering study staff member prior to the start of each interview and focus group.

## Retention and withdrawal

To enhance participant retention in the study, the research team will provide convenient and flexible scheduling with easily accessible study locations. Regular check-ins will also be conducted.

All participants will be free to withdraw from the study at any time, for any reason without affecting their usual care or work arrangements (peer workers). Multiple ways to communicate this intent to withdraw will be provided, and processes will be made available, for the participant’s preference. Where relevant, the withdrawing participant will be offered a wrap-up session with their peer worker or GP.

Participants may be withdrawn from the study due to any adverse event associated with their involvement in the PS-PC sessions, where it appears unsafe to continue or results in a serious adverse event where their condition worsens such that they require treatment or hospitalisation for an acute psychiatric episode or other health condition. The worsening of a co-occurring medical or physical condition will only cause the participant to be withdrawn if this significantly impact the participant’s ability to attend sessions. Withdrawals performed by study staff will require deliberation, especially where a participant experiences a worsening of mental health, as withdrawing the participant would lead to a reduction of support when it may be most needed. Where possible, the severity of these withdrawal reasons will be recorded.

## Data privacy and management

Stringent measures will be implemented to ensure the privacy and confidentiality of the participants. Unique study identifications will be assigned to participants to de-identify all responses across longitudinal data collection. All databases will be protected using password and two-factor authorisation encrypted access systems. Because involvement in the trial is short-term and not overly invasive for each participant, and the known risks associated with this intervention are minimal, a data monitoring committee is not necessary. Likewise, there are no plans for interim analyses or development of stopping guidelines.

All identifiable data (consent forms, etc.) will be de-identified and filed with the study documents during the recruitment period. At completion of the study, all participant forms will be sent to the coordinating site by registered mail, for collation and archiving. All participant files will be reconciled and stored along with all study materials—both hard copy and electronic—consistent with the regulations of the Government of South Australia regarding the retention and disposal of participant records.

## Project oversight

The study will be supervised by PRG and SRG. The PRG will oversee project implementation; its membership includes Chief and Associate Investigators and project staff. SRG membership is via PRG invitation and includes community stakeholders with to ensure their perspectives, especially lived experiences, are integrated during project implementation.

### Monitoring

The PRG will be responsible for monitoring the conduct of the study including all adverse events; they will be guided by a Standard Operating Procedure (SOP) which defines adverse events and study related responses. As this is a pragmatic trial being conducted in primary care, any harms will be non-systematically identified through spontaneously reporting by either the participant or peer worker. Incidents will be escalated to the participant’s treating GP who will perform a clinical assessment of risk. All adverse events will be reported to the Flinders University HREC and included within any reported findings. No independent auditing of trial conduct will be undertaken.

Regular communication between research staff and care providers (GPs, practice managers, peer coordinators, peer workers) will be instrumental in key information being shared with relevant persons. Where amendments to the protocol require discussion (i.e., major changes are necessary), the PRG will be consulted. Key Performance indicators have been developed to track study process to ensure recruitment and follow-up are completed within specified timeframes.

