**Methods:**

This stepped-wedge cluster randomised controlled trial (RCT) aims to evaluate a lived experience peer support intervention for accessing mental health care in primary care (PS-PC). Four medical practices across Australia will be randomly allocated to switch from control to intervention, until all practices are delivering the PS-PC intervention. The study will enrol 66 patients at each practice (total sample size of 264). Over a period of 3–4 months, 12 h of practical and emotional support provided by lived experience peer workers will be available to participants. Scale-based questionnaires will inform intervention efficacy in terms of mental health outcomes (e.g., self-efficacy) and other health outcomes (e.g., healthcare-related costs) over four time points. Other perspectives will be explored through scales completed by approximately 150 family members or carers (carer burden) and 16 peer workers (self-efficacy) pre- and post-intervention, and 20 medical practice staff members (attitudes toward peer workers) at the end of each study site’s involvement in the intervention. Interviews (*n* = 60) and six focus groups held toward the end of each study site’s involvement will further explore the views of participants, family members or carers, peer workers, and practice staff to better understand the efficacy and acceptability of the intervention.

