**Fig. 2 Fig2:**
[figure not shown]
Intervention stages and flow of care

The initial meeting between the participant and peer worker will provide an opportunity to refine and mutually agree on the support plan. Support may entail emotional and practical assistance, phone calls, home visits, community linkage, and sharing of strategies to enhance lifestyle behaviour (e.g., social connection, physical activity, stress management) to build self-efficacy and self-care and to set recovery goals.

Peer workers will provide 8–12 h of support per participant over approximately 2–3 months, with the option to extend for 2–3 months if needed. If desired, participants may also cease receiving peer worker support sessions prematurely, if they feel they have gained sufficient benefit from these sessions. At the completion of the intervention, the peer worker and participant will identify supports that are relevant and available and the peer worker will link the participant with those supports. The peer worker will provide a summary of trial activities to the participant and their GP. This is intended to be used for discussion in a primary care appointment to facilitate ongoing continuity of care.

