## Primary outcome measures

The primary outcome will be change in a person’s self-efficacy measured by the GSE [32]. The GSE is a reliable (*α* = 0.76 to 0.90), validated, ten-item unidimensional self-report scale used to assess self-efficacy within general adult populations. The scale conceptualises self-efficacy as a person’s perceived ability to cope and adapt in the face of both daily hassles and more stressful life events. Respondents indicate how much a given item applies to them from 1 (not at all true) to 4 (exactly true), with total possible scores of 10–40 (higher scores indicate greater self-efficacy). The scale was originally designed to assess change occurring over the course of a trial and is also used in CMO contexts as an indicator of client well-being. This tool will be used to inform intervention efficacy for participants at baseline, 3 months post-baseline, 6 months post-baseline, and 9 months post baseline. For all measures taken at multiple time points, the comparison between care as usual (baseline) and post-intervention (3 months post-baseline) will be of primary importance, whilst following time points will inform the longevity of any intervention-related effects.

All baseline measures, including the GSE, will be administered as a questionnaire by a practice nurse following screening and consent procedures. During the final session of peer support, the peer worker will assist the participant with completing the 3-month post-baseline measures. All further follow-up measures will be administered as a questionnaire either through REDCap or a telephone call from study staff depending on participant preference.

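### Harms are identified only by spontaneous report from the participant or peer worker, and the peer worker is present for only part of follow-up, so adverse-event counts are likely incomplete and not comparable between phases

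*Protocol article*

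**What the plan says.** Under Monitoring, the article gives the pragmatic primary-care setting as its reason and says that "any harms will be non-systematically identified through spontaneously reporting by either the participant or peer worker". The same section commits that "All adverse events will be reported to the Flinders University HREC and included within any reported findings". It mentions a standard operating procedure, not shown, and describes it as covering the definition of adverse events and the responses to them.

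Randomisation says that peer support is added to usual care once a site switches. Intervention says that support is given "over approximately 2–3 months, with the option to extend for 2–3 months if needed", and that "participants may also cease receiving peer worker support sessions prematurely". The abstract gives a different duration: "Over a period of 3–4 months, 12 h of practical and emotional support".

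Primary outcome measures sets the assessments at "baseline, 3 months post-baseline, 6 months post-baseline, and 9 months post baseline". The peer worker helps the participant complete the 3-month forms; later forms go through REDCap or a telephone call from study staff. Retention and withdrawal adds "Regular check-ins will also be conducted", as a means of keeping participants in the study. No assessment or check-in is named as a source of harm data.

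**The concern.** Passive reporting usually finds fewer events than asking. Here there is a second difficulty: the number of people who can report depends on exposure. While support runs, two named reporters can raise an event. Before the site switches and after the last session, only the participant can. Extension is given according to need, and early stopping is allowed when a participant feels enough has been gained, so the length of two-reporter capture may also vary with how well the participant is doing.

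The events at issue are not trivial. The withdrawal rule foresees participants whose condition worsens so that "they require treatment or hospitalisation for an acute psychiatric episode or other health condition". The article plans no data monitoring committee and no independent audit, so the reported adverse events are the main safety evidence the trial will produce. If a reader sets events during support beside events before or after it, a difference in detection opportunity can pass for a difference in harm.

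**Working it through.** The article gives no figure for harm ascertainment, so there is none to reproduce. The check is how much of follow-up has the second reporter.

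**Inputs**
- Follow-up: 9 months from baseline (Primary outcome measures).
- Support, standard: 2–3 months (Intervention).
- Support with full extension: 2 + 2 = 4 to 3 + 3 = 6 months (Intervention).
- Support as given in the abstract: 3–4 months.
- Assumption: support starts at baseline and runs without a gap. A later start within the 9 months moves the covered period; early stopping shortens it.

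**Formula:** share without a peer worker = (9 − months of support) / 9.

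| Duration used | Months with peer worker | Months without | Share without |
|---|---|---|---|
| Intervention, standard | 2–3 | 6–7 | 6/9 = 67% to 7/9 = 78% |
| Abstract | 3–4 | 5–6 | 5/9 = 56% to 6/9 = 67% |
| Intervention, full extension | 4–6 | 3–5 | 3/9 = 33% to 5/9 = 56% |

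In any time enrolled before the site switches, the peer-worker route is absent altogether. The article gives no length for that time.

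**Direction of the inequality.** Let p be the chance that a participant volunteers an event and q the chance that the peer worker reports one the participant did not. Detection is p without a peer worker and p + (1 − p)q with one. The second is larger whenever q > 0 and p < 1, provided that having a peer worker does not make the participant less likely to report. The document gives neither p nor q, so the direction can be argued but the size cannot be calculated.

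**Existing contacts that could carry a question.** The questionnaires at 3, 6 and 9 months are already scheduled. A service-use questionnaire also exists, but its timing is inconsistent: Health outcomes and health services utilisation lists all four time points, whereas Table 1 lists service-use costs after the intervention (t1) only.

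**The case against.** The method is disclosed, a reason is given, and the article regards the known risks as minimal. Statistical methods plans no adverse-event rate and no contrast between phases; the promise is only to include events in the findings. Usual-care time may be short, since the article equates care as usual with baseline and schedules nothing before the switch beyond enrolment or baseline. Check-ins, staff telephone calls and routine exchange between research staff and practices could all bring events to light, and their content is not shown. The procedure document may add detail.

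Much of this stands, and it rules out stronger readings that a reader might infer:
- *That harms go largely unseen, or that the count is wrong.* Participants can report throughout, and no reporting probability is given. Likely incomplete is as far as the text goes.
- *That there is no peer worker for most of the 9 months.* This holds for standard support and for the abstract's duration, but with the full extension the range is 33–56%.
- *That the trial will show peer support as more harmful than usual care by some given ratio.* No such comparison is planned, and any ratio would rest wholly on assumed probabilities.
- *That GP chart audit could fill the gap.* The article describes it for prospective participants' demographics and diagnosis, not as a follow-up contact.
- *That the hospitalisation wording is a general reporting definition.* It belongs to a withdrawal rule that opens with events linked to the support sessions.

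What does not stand is the appeal to missing detail. The article itself fixes how harms are identified, and the procedure document is described as covering definitions and responses, not identification. The pragmatic setting is a weak reason, because structured questionnaires are already given at 3, 6 and 9 months.

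**Conclusion.** The point holds in a limited form. Ascertainment of harms is passive by the article's own statement, and the opportunity for detection is tied to exposure: one of the two reporters is absent before the switch and for 33–78% of the 9 months after baseline, depending on the duration of support. The counts are therefore likely to be incomplete and should not be compared across phases. The percentages assume that support starts at baseline and is continuous. The number of events missed and the size of any distortion cannot be derived from the document. The primary outcome is not affected. This is a cheap improvement to safety reporting, not a flaw in the main analysis.

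**What to change.** Amend the Monitoring section as follows.

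1. Ask every participant the same fixed adverse-event question, including any emergency or hospital attendance since the last contact, on the existing 3-, 6- and 9-month questionnaires. Add it to the enrolment or baseline questionnaire to cover any time enrolled before the switch.
2. Have the 3-month item completed by the participant alone or asked by study staff, because the peer worker otherwise assists with that form.
3. Keep spontaneous reports, tabulated as a separate source.
4. Present events descriptively by phase (before the switch, during support, after support) with person-time, and state that spontaneous counts are not comparable between phases.
5. Use the service-use questionnaire as a further source only after the text and Table 1 are reconciled on when it is collected. The support durations in the abstract and the Intervention section also need reconciling, since the phase boundaries depend on them.

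The cost is one or two items on forms already in use, a small change to how one 3-month item is completed, and a wording amendment. The downside is more minor events to log and report to the ethics committee.

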## Statistical methods

Independent sample *t*-test and standard Chi-square test for association with continuity correction will compare participant characteristics during usual care with those during mid- and post-intervention. Multivariate multilevel mixed-effects models will be used to examine changes in outcome measures between pre-intervention baseline and post-intervention follow-up over time (6, 12, and 18 months) including interactions between pre-intervention baseline and post-intervention follow-up over time. The comparison between care as usual (baseline) and post-intervention (3-months post-baseline) will be of primary importance, whilst subsequent time points will inform the longevity of any intervention-related effects. This analytical strategy is selected due to the hierarchical nature of the data, where participants are nested within practices. Linear models will be used for continuous outcomes (i.e., GSE, K10, RAS-DS, YES, EQ-5D-5L, TFA) and logit models for binary outcomes (e.g., demographics, diagnosis, etc.). The two-sided test will be performed for all analyses, 95% confidence interval reported, and level of significance set at *p* < 0.05. All analyses will be performed using Stata software version 16.1 and R version 4.1.1. Responses on the EQ-5D-5L integrated with survival curves will be integrated estimate quality adjusted life years using the quality-adjusted survival analysis method. Participant self-reported service use during usual care will be compared with those during and post-intervention to determine within-trial incremental costs and trial effectiveness. Where there is missing data, intention-to-treat protocol will be followed for all participants who receive peer support, where baseline information is available. If there is a significant amount of missing data (missing at random), multiple imputation will be used.

The CFIR menu will guide coding using a descriptive content-coding approach that is both deductive and inductive [38]. Two researchers will independently code each transcript then compare, with any differences resolved through a third analyst. Ratings of valence and manifestation will also be assigned to codes for rigor, and the ‘coherence’ of the data will support its validity [39]. If it is determined that additional data are required for saturation of themes, further data collection will be conducted. Researchers conducting these phases of analysis will be blinded to the general practice that participants attend [40]. The qualitative study will inform analysis and interpretation of the quantitative study findings.

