## Sample size

The sample size calculation (*n* = 264 participants; 66 per practice) is based on the primary outcome of the self-efficacy score from an RCT assessing the effectiveness of peer support for mental health outpatients in Germany [29]. Adjusted scores significantly improved by an average of 1.77 points (95% CI 0.02–3.53) in the peer support group compared to usual care (mean score = 24.3, pooled SD = 7.2) in the 6-month follow-up. As this study is based on 9-month follow-up, the upper confidence level of the improved score will be used. Assuming a 10% attrition rate, we will need to recruit 66 participants per practice with a total of 264 participants. This achieves at least 80% power to detect a difference of mean self-efficacy score of 3.53 points. A power and sample-size analysis for hypothesis test from Stata version 16.1 was used to calculate the sample size*.* The test statistic used is the one-sided Wald *Z*-test and the significance level of the test is 0.05. Assuming heterogeneity amongst practices and substantial differences (i.e., minimal resemblance) in participants at each site, the responses of participants will not be significantly influenced by their enrolment at a particular practice. As such, the ICC is 0.01.

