## Intervention

Each participant allocated to the intervention will be matched by a ‘peer coordinator’ (a champion peer worker coordinating between peer workers and the study staff) to the skills and experience of a peer worker. The main intervention steps and the flow of health care providers can be seen in Fig. 2.

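### The stated hierarchy and ICC leave out the peer worker; if outcomes vary by worker, the standard error of the baseline-to-3-month change will be understated

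*Protocol article*

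**What the plan says.** **Model.** Statistical methods: "Multivariate multilevel mixed-effects models will be used to examine changes in outcome measures". The reason given for a multilevel model is "due to the hierarchical nature of the data, where participants are nested within practices". The random effects are not listed.

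**Primary comparison.** The same section says: "The comparison between care as usual (baseline) and post-intervention (3-months post-baseline) will be of primary importance". The Primary outcome measures section says the same.

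**Sample size.** "we will need to recruit 66 participants per practice with a total of 264 participants". The only ICC is 0.01, and it is argued entirely from how far practices influence responses.

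**Delivery.** Under Intervention, a coordinator matches each participant "to the skills and experience of a peer worker". The text after Fig. 2 adds: "Peer workers will provide 8–12 h of support per participant over approximately 2–3 months".

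**Measurement.** Primary outcome measures: in the last support session, "the peer worker will assist the participant with completing the 3-month post-baseline measures".

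**Number of workers.** The only figure is in the abstract, as the number completing a scale: "16 peer workers (self-efficacy) pre- and post-intervention".

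**The concern.** Peer support is delivered by individuals, and the Introduction describes its active ingredient as the worker's own recovery experience. Some variation between workers in effect is therefore plausible. The worker's help with the 3-month forms is a second possible source of similarity among participants of the same worker, at the time point that matters most.

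Both sources begin after baseline. The grouping that the plan names, practice, is present before and after. If participants of the same worker change alike and the model has no term for it, their changes are counted as independent. The confidence interval is then too narrow and the test rejects too often. The Discussion says a positive result may support public funding of peer workers, so the precision claimed for the main estimate matters.

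**Working it through.** **1. The plan's own figure.** Inputs from Sample size: difference 3.53, SD 7.2, one-sided 0.05, 80% power, practice ICC 0.01, attrition 10%. The layout is my assumption: a cross-sectional stepped wedge (Hussey–Hughes) with 4 practices, 4 steps and 5 periods.

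- 12 per practice-period gives 12 × 5 = 60 per practice, with SE 1.419.
- Power = Φ(3.53/1.419 − 1.645) = 80.0%.
- Attrition: 60 × 1.10 = 66, as stated (60/0.9 would give 67).
- A parallel comparison of two practices against two does not reproduce it: 35 per practice, 39 with attrition.

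The stated size is therefore reached with practice clustering alone.

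**2. Why the named levels do not help.** Write the two scores of a participant as

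- baseline: μ + practice + participant + e0
- 3 months: μ + δ + practice + participant + worker + e1

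The change is δ + worker + (e1 − e0). Practice and participant intercepts cancel and the worker effect stays. A practice-level random slope would take up part of it, but none is stated and it would rest on four practices.

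**3. Size for the primary comparison.** Analysed participants: 264 × 0.9 = 237.6. Per worker, assuming 16 workers with equal caseloads: m = 237.6/16 = 14.85. Let ρ be the worker's share of the variance of the change (assumed). Then

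- design effect DE = 1 + (m − 1)ρ = 1 + 13.85ρ
- true SE / model SE = √DE
- actual two-sided type I error = 2[1 − Φ(1.96/√DE)]

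| ρ (assumed) | DE | SE factor | Type I error |
|---|---|---|---|
| 0 | 1.00 | 1.00 | 5.0% |
| 0.01 | 1.139 | 1.07 | 6.6% |
| 0.02 | 1.277 | 1.13 | 8.3% |
| 0.05 | 1.692 | 1.30 | 13.2% |
| 0.10 | 2.385 | 1.54 | 20.4% |

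Simulation with 16 × 15 participants and an assumed pre-post correlation of 0.5 gave factors of 1.07 to 1.55 and errors of 6.7% to 20.4% for ρ from 0.01 to 0.10. Fitting a mixed model with practice and participant intercepts to simulated data at ρ = 0.05 (150 runs) gave a factor of 1.27 and an error of about 13%. This agrees with step 2.

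In scale points: with SD 7.2 and correlation 0.5, the variance of the change is 2 × 7.2² × (1 − 0.5) = 51.84. The model SE is then 7.2/√237.6 = 0.47 points. At ρ = 0.05 the worker SD is √(0.05 × 51.84) = 1.61 points and the true SE is 0.47 × 1.30 = 0.61.

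**4. Size for a stepped-wedge contrast.** Same layout as step 1, four workers per practice, worker ICC now a share of the post-intervention score variance.

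| Worker ICC (assumed) | SE factor | Type I error | One-sided power with worker modelled |
|---|---|---|---|
| 0 | 1.00 | 5.0% | 80.0% |
| 0.01 | 1.01 | 5.2% | 79.4% |
| 0.02 | 1.02 | 5.4% | 78.8% |
| 0.05 | 1.05 | 6.1% | 77.1% |
| 0.10 | 1.09 | 7.2% | 74.6% |

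The effect is small here.

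**The case against.** **The sentence is a rationale, not a specification.** It explains why a multilevel model was chosen and does not even mention repeated occasions within participant. The random-effects list may stand in an analysis plan that is not shown, and nothing in the article excludes a worker term. This stands as a limit: one cannot say that the plan rules the term out. But the article does state the data hierarchy and the ICC, and both omit a level that its own intervention creates. An analysis that follows what is written would lack the term.

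**The inputs are inferred.** Sixteen is the number completing a scale, which the Eligibility criteria section makes voluntary, so more workers may deliver support and caseloads would then be smaller. One worker per participant throughout and equal caseloads are readings, not statements; unequal caseloads would raise the inflation. All of this stands, and the size is given only as a range.

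**A reader might infer that the standard errors are too small as a matter of fact.** The documents do not support that. It needs a positive worker ICC, which they do not report.

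**A reader might also infer that the trial effectively has 16 observations rather than 264.** The arithmetic does not bear this out. With 240 analysed and 15 per worker, the design effects are 1.14, 1.28, 1.70 and 2.40, so the effective sizes are 240/1.14 = 211, 188, 141 and 100. An effective size near 16 would need an ICC near 1.

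**The contrast matters.** A stepped-wedge between-condition estimate is barely affected. That is right, but the protocol twice gives primary importance to the within-participant change, where the effect is larger.

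**Conclusion.** The point holds conditionally. The stated hierarchy and the single practice ICC leave out the peer worker, and the terms that are named cannot absorb a worker effect on the baseline-to-3-month change. If outcomes vary by worker, the SE of that change is understated: by a factor of about 1.07 to 1.55, with a two-sided type I error of about 7% to 20%. This rests on assumed worker ICCs of 0.01 to 0.10, about 16 workers, about 15 analysed participants each, and no practice-level slope. At an ICC of 0 there is no error. For a stepped-wedge contrast the factor is about 1.01 to 1.09. The plan should be changed because the correction is cheap and the primary comparison is the exposed one, not because the size is known.

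**What to change.** Record the peer worker's ID for every participant, including any change of worker. Add a random peer-worker effect that acts only on post-intervention measurements (a partially nested term). Nest it in practice, or cross it with practice if workers serve more than one; the community organisations that employ them may make this possible. Use a small-sample degrees-of-freedom correction such as Satterthwaite or Kenward–Roger. Put the term in the primary model, or at least in a pre-specified sensitivity analysis, and report the worker-level variance.

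**Cost.** One data field, already known from the matching step but possibly hard to recover later, and one variance term. The confidence interval may widen somewhat. The variance will be imprecise with few workers. Because matching is deliberate rather than random, it will also mix differences between workers with differences between the participants they were given, and the report should say so.
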